### 3.4 Algorithm indicators

In both study conditions, the respective algorithms will alert subjects about their real-time health status in the Ava COVID-RED app through 3 types of indicators:

- **Green light:** No deviations in physical health (symptoms or biophysical parameters) detected. No recommendation is given to the subjects.
- **Yellow light:** Subjects are experiencing some symptoms but not those strictly defined as related to COVID-19 or biophysical parameters deviate slightly from baseline but do not meet the threshold value for a Red light indicator. The Yellow light indicator asks participants to consider self-isolating and keeping an eye on the Ava COVID-RED app the following day.
- **Red light:** Significant changes in biophysical parameters have been detected or symptoms that meet the RIVM criteria have been reported. The Red light indicator suggests subjects consider getting tested for COVID-19 and/or to consult a medical professional.

In all cases of a red-light indicator, subjects will receive the following generic message on the home screen of the Ava COVID-RED app after synchronising their bracelet or logging their symptoms within the last 24 hours:

“Your data suggests changes in physiological parameters and/or symptoms that might be related to a potential COVID-19 infection. Please consider seeking testing and/or input from a medical professional.”

When subjects obtain a positive PCR/antigen or serology test result during the study, they will continue to be in the study but will be moved into a so-called “COVID-positive” mode in the Ava COVID-RED app. This means that they will no longer receive recommendations from the algorithms but can still contribute and track symptom and bracelet data.

### **3.5 SARS-CoV-2 infection testing**

This study will use the existing testing infrastructure in the Netherlands provided by the Municipal Health services (GGD). At the time of writing, any citizen of the Netherlands has access to free polymerase chain reaction (PCR) or antigen testing for SARS-CoV-2 if they experience any of the specific symptoms defined by the RIVM guidelines (at the time of writing, these include: common cold symptoms [such as a nasal cold, runny nose, sneezing, sore throat], coughing, shortness of breath, elevated temperature or fever, and sudden loss of smell and/or taste [without nasal congestion]). As per 1 December 2020, asymptomatic persons who have been in close contact with someone who tested SARS-CoV-2-positive (as determined by the GGD contact-tracing program or by the CoronaMelder app) will also qualify for testing. SARS-CoV-2 virus testing procedures at the GGD (types of tests and criteria for testing) may change during the study period; up-to-date testing guidelines are always available on the RIVM website; <https://www.rivm.nl/>. During the study, subjects will be instructed to use GGD testing where possible and appropriate because this will automatically enter them into the national contact-tracing program. The results of the GGD test will be communicated to the subject directly through a web portal or by phone, as is done on a national level for every individual who gets tested. Changes in national testing policy and the types of tests used regionally will be monitored and taken into account where appropriate.

All subjects who receive a red light indication to get testing will be instructed to first contact the GGD for testing. If they do not satisfy the criteria for GGD testing, subjects can use nasal swab sampling kits provided by the study team to collect a sample themselves which they will send to the central study laboratory for testing using provided return envelopes. Subjects will be asked to log all SARS-CoV-2 test results into the Ava COVID-RED app regardless of where the testing was done. Additional details surrounding the location, accessibility and

types of tests will be requested through periodic surveys. The study team will report all subjects who tested positive to the GGD (SARS-CoV-2 is a notifiable disease in the Netherlands) so that the GGD can initiate contact-tracing.

### **3.6 Serology testing for SARS-CoV-2**

Subjects will also be asked to donate fingerprick blood for SARS-CoV-2 serology (antibody) testing at baseline, at the end of the Learning Phase (depending on when they entered the study), and at the end of each period to determine if and when (during which period) they became infected with SARS-CoV-2. Baseline samples of subjects will only be analysed if the sample collected at the end of the Learning Phase is positive for SARS-CoV-2 antibodies or if the subject entered the study at the end of the recruitment Period. Samples of subjects collected at the end of Period 1 will only be analysed if the sample collected at the end of Period 2 is positive for SARS-CoV-2 antibodies. Given the likelihood that subjects will be vaccinated during follow-up (see Section 3.7), differentiation between antibodies produced following a COVID-19 vaccination or antibodies produced as a result of a natural infection by the SARS-CoV-2 virus is essential. This is especially important during Period 2 when evaluation of the V2 algorithms takes place. All approved COVID-19 vaccines and likely candidates still being developed or evaluated at the time of writing elicit an immune response against the virus spike (S) protein resulting in antibodies directed against the S-protein. Natural infections elicit an immune response resulting in antibodies against the virus S-protein and Nucleocapsid (N)-protein. Due to logistical limitations in the short term, anti-S antibody serology tests will be used for baseline and Learning Phase samples, while anti-N antibody serology tests will be used for the Period 1 and Period 2 samples.

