During the study, the algorithms in both the control and experimental conditions will provide real-time prediction to subjects whether they likely have an active SARS-CoV-2 infection. Individuals with a suspected SARS-CoV-2 infection based on these algorithms will be encouraged to get tested using the existing testing infrastructure in the Netherlands provided by the Municipal Health services (GGD). At the moment of writing, the GGD offers free SARS-CoV-2 polymerase chain reaction (PCR) and antigen testing services. While in this protocol tests to confirm current SARS-CoV-2 infection are described as PCR and/or antigen tests, results from other validated testing methods used by the GGD will also be documented and processed in the same way, should the GGD choose to expand the type of tests being used to detect SARS-CoV-2 infection in Dutch residents. Subjects who are thought to have an SARS-CoV-2 infection according to the algorithm of the control or experimental condition, but are rejected for testing by the GGD, will be advised to use self-sampling kits provided by the study team which they can send to the central laboratory for testing. A reason for such rejection by the GGD may include not (yet) having overt symptoms of a respiratory tract infection plus not having any evidence (such as a GGD or CoronaMelder app notification) of having been in close contact with someone who tested SARS-CoV-2-positive. In addition, fingerstick capillary blood samples will be collected from COVID-RED subjects at baseline, after the Learning Phase (if applicable) and after the completion of each period. Samples collected after the Learning Phase and the completion of Period 2 will be tested for SARS-CoV-2 antibodies to determine whether the subject had a previous SARS-CoV-2 infection prior to the study or during the test periods (which was not detected through real-time SARS-CoV-2 infection testing). Baseline samples of subjects will only be analysed if the sample collected at the end of the Learning Phase is positive for SARS-CoV-2 antibodies or if the subject entered the study at the end of the recruitment Period. Samples of subjects collected at the end of Period 1 will only be analysed if the sample collected at the end of Period 2 is positive for SARS-CoV-2 antibodies.

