## 8. METHODS

### 8.1 Study parameters/endpoints

Note that for each parameter and endpoint listed in 8.1.1 and 8.1.2 the measure will be observed in Period 1 and in Period 2. The parameters and endpoints will be statistically assessed within each period separately. See Section 10 for additional details. For the assessment schedule, see APPENDIX 1. Details on the assessments are provided in Section 8.4.

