#### **8.4.8 Collection & testing of plasma/blood sample**

Subjects will be asked to self-collect a capillary blood sample using provided materials at Baseline as well as upon completion of the Learning Phase, Period 1 and Period 2 by fingerprick for up to a total of 4 samples during the study. Subjects entering the study at the end of the recruitment Period will have a total of 3 samples, they will be asked to self-collect a sample at Baseline as well as upon completion of the Period 1 and Period 2.

Subjects will be requested to send the sample to the central laboratory within 24 hours using provided, pre-addressed medical envelopes with prepaid postage. The samples will be processed and stored at the central laboratory on the day of receipt. All samples collected at the end of the Learning Phase, and Period 2 will directly be tested for SARS-CoV-2 antibodies using an in-house ELISA method upon receipt. By testing at the end of each stage of the study, we have nearly 100% knowledge of infection status at the end of each trial period, thereby allowing assessment of sensitivity and specificity. Baseline samples will only be analyzed if the sample collected at the end of the Learning Phase is positive for SARS-CoV-2 antibodies or if the subject entered the study at the end of the recruitment Period. Samples collected at the end of Period 1 will only be analyzed if the sample collected at the end of Period 2 is positive for SARS-CoV-2 antibodies. In this way, subjects who had a SARS-CoV-2 infection prior to participation in the study or at start of Period 2 can be identified. The central laboratory in-house ELISA method assesses total SARS-CoV-2 antibodies (Ab), and if positive, isotype-specific (IgM and IgG) SARS-CoV-2 antibodies. Note that anti-S antibody serology tests will be used for baseline and Learning Phase samples. Anti-N antibody serology tests will be used for the Period 1 and Period 2 samples. Subjects will be informed on their testing result for SARS-CoV-2 antibodies.

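### The stored Period 1 blood sample is assayed only after a positive Period 2 sample, so subjects who gave a Period 1 sample but no usable Period 2 sample lose their Period 1 serostatus

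*Protocol*

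**What the plan says.** Section 3.6 says blood is collected at the end of each period "to determine if and when (during which period) they became infected with SARS-CoV-2". The Period 1 sample, however, "will only be analysed if the sample collected at the end of Period 2 is positive for SARS-CoV-2 antibodies". Section 1.4 gives the same rule, and so does Section 8.4.8: "Samples collected at the end of Period 1 will only be analyzed if the sample collected at the end of Period 2 is positive". None of the three says what happens when no Period 2 sample arrives or when it cannot be read. The baseline sample, by contrast, has a second trigger, for late entrants.

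On receipt, "The samples will be processed and stored at the central laboratory on the day of receipt" (8.4.8). The same section concludes that, because testing is done at the end of each stage, "we have nearly 100% knowledge of infection status at the end of each trial period".

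Period 1 status is needed. Section 8.1 says: "The parameters and endpoints will be statistically assessed within each period separately". Section 10.2 asks for the ever-infected analysis within each period and also for both periods combined. The bootstrap in 10.4 takes Period 1 serology as the true outcome (Table 6).

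**The concern.** Deferral saves assays only if the later sample turns up. A sample that was never returned is not positive, so under the rule as written the stored Period 1 sample is never assayed, and nothing can be inferred about it either.

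Missing Period 2 samples are foreseeable. Sampling is remote and self-administered. Section 8.5.1 lists loss to follow-up, withdrawal of consent and removal for compliance below 20%. Section 8.6 allows no replacement, and the general approach in Section 10 expects missing data.

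Two things are at stake:

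- **Confirmed negatives.** Section 10.2 defines condition negative (in its Period 2 form) as no positive virus test and negative serology. Without serology a subject cannot be a confirmed negative, and subjects whose status cannot be determined are left out of estimation.
- **Silent infections.** An infection that prompted no virus test is visible only in serology. Virus testing is largely prompted by red lights (3.5, 8.4.12). If virus-test positives without serology are retained, the infections that remain are enriched for those the algorithm flagged.

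**Working it through.** **1. The protocol's own case.** Let *d* be the share of subjects without a usable Period 2 sample.

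- Period 2 negative: Period 1 is taken as negative (this assumes antibodies persist through Period 2).
- Period 2 positive: the Period 1 sample is assayed.
- Period 2 missing: Period 1 serostatus is unknown.

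The known share is therefore at most 1 − *d*. It is a maximum because a Period 2 positive with no Period 1 sample is also unresolved. The weighting example in 10.4.2 assumes no dropout, so *d* = 0 and the known share is 100%. That agrees with 8.4.8, but only under full sample return.

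**2. With samples missing.** The protocol states no rate, so *d* is an assumption. Inputs: 20,000 subjects (3.1); 500 + 600 = 1,100 illustrative Period 1 infections (10.4.2), or 1,100 / 20,000 = 5.5%, taken to be equally common among those without a Period 2 sample.

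| *d* (assumed) | Known, at most | Unknown = 20,000 × *d* | Infections among them (5.5%) |
|---|---|---|---|
| 2% | 98% | 400 | 22 |
| 5% | 95% | 1,000 | 55 |
| 10% | 90% | 2,000 | 110 |
| 20% | 80% | 4,000 | 220 |
| 30% | 70% | 6,000 | 330 |

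The last two columns are upper bounds on what the assay rule costs. Some of these subjects left before giving a Period 1 sample, and some infections will have a positive Period 1 virus test.

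**3. Weight of Period 1 in the combined analysis.** With the weights printed in 10.4.2: 10,000 / (10,000 + 8,900) = 53%. The 8,900 subtracts both sequences' infections from one sequence's size. With per-sequence sizes of 9,500 and 9,400 the share is 20,000 / (20,000 + 18,900) = 51%. Either way it is about half.

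**4. Direction of bias, if virus-test positives without serology are kept.** Let *S* be true sensitivity, *c* the chance of virus-test confirmation for an infection that drew a red light, and *u* the chance for one that did not.

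Observed sensitivity = [*S*(1 − *d*) + *d·S·c*] / [(1 − *d*) + *d*(*S·c* + (1 − *S*)*u*)]

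With all rates assumed (*S* = 70%, *c* = 60%, *u* = 10%):

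- *d* = 10%: 0.672 / 0.945 = 71.1%
- *d* = 20%: 0.644 / 0.890 = 72.4%
- *d* = 30%: 0.616 / 0.835 = 73.8%

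With *S* = 50% and the same *c* and *u*, *d* = 20% gives 52.9%. A true gap of 20 points between conditions would then appear as 72.4 − 52.9 = 19.5 points. The contrast moves less than the individual sensitivities as long as *d*, *c* and *u* are the same in both conditions.

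**5. Effect of the added trigger.** Let *r* be the share of those without a Period 2 sample who have a stored Period 1 sample (assumed). The known share becomes 1 − *d* + *d·r*. For *d* = 20% it rises from 80% to 90% (*r* = 0.5), 96% (*r* = 0.8) or 100% (*r* = 1).

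**The case against.** **The primary comparison is in Period 2.** Sections 10 and 10.2 place it there, and Section 10 gives Period 1 a supporting role. A subject without a Period 2 sample has no end-of-Period-2 serology whatever is done with the Period 1 sample. This stands. The only route into the primary analysis is narrow: someone classified by a Period 2 virus test without Period 2 serology, including a subject who dies in Period 2, whose stored Period 1 sample might have shown an earlier infection and led to exclusion.

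**Not everyone without a Period 2 sample loses a Period 1 status.** A reader might infer that they do. Subjects who left before the end of Period 1 have nothing stored, and infection is defined by virus test or serology, so a positive Period 1 virus test can still make a case. What is lost is the serological status.

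**Infected subjects dropping out because their indicators stop.** A reader might offer this as the reason for informative loss. It does not fit Sections 3.4 and 8.4.13: COVID-positive mode follows a positive result, so it applies to people whose infection is already documented, and they are asked to continue. An infection visible only in an unassayed sample changes nothing in the app.

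**The upward bias depends on a reading of 10.2.** One paragraph takes serology as the standard for living subjects and excludes the rest. The definition of condition positive accepts a virus test alone. Under the first reading all subjects without serology fall out, and the selective retention in step 4 does not arise. The loss of subjects remains.

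**Missing data are provided for.** Section 10 foresees imputation and defers detail to the analysis plan, and 8.7 provides back-up contacts. Neither creates an assay result. The trigger is a laboratory instruction and belongs in the protocol.

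**Conclusion.** The gap is real and limited. Three sections state a rule with no branch for a missing Period 2 sample, and following it discards Period 1 serostatus that could be read from stored blood. The Period 1 analyses and the combined-period bootstrap are affected, the latter with about half its weight on Period 1. The primary Period 2 comparison is affected only at the margin.

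The size cannot be fixed from the protocol. Up to 400 to 6,000 of 20,000 subjects is an upper bound over an assumed 2% to 30% of missing samples. The sensitivity figures are an illustration in which every rate is assumed.

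A reader might also conclude that the protocol's figures refute the sentence in 8.4.8. They do not: at 2% missing, 98% known is still close to complete. The sentence is unsupported, because it rests on testing at the end of each stage when Period 1 samples are not routinely tested and their status depends on a later sample.

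**What to change.** In Sections 1.4, 3.6 and 8.4.8, add that the stored Period 1 sample is also analysed when the Period 2 sample is missing or unusable. In 8.4.8, make the statement about knowledge of infection status conditional on sample return.

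The cost is extra assays on blood already held, with no new sampling. Their number is at most the number of Period 2 assays not run or unusable. For example, at an assumed 20% missing with 80% of those having a stored sample, it is 20,000 × 0.20 × 0.80 = 3,200. The protocol gives no assay price. For subjects who withdraw consent, the clause applies only as far as the consent terms allow.

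A parallel clause for the baseline sample when the Learning Phase sample is missing is optional. It would show status at entry and not at the start of Period 1. Because that assay is anti-S and vaccinated subjects are eligible, a positive result would have to be read with vaccination status.

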### **3.7 COVID-19 Vaccines**

As of December 2020, the first of several vaccines developed specifically for COVID-19 have been approved by the European Medicines Agency (EMA). Like many other countries the government of the Netherlands is aiming to vaccinate the majority of its population by the end of 2021. Given the differences in effectiveness between manufactured vaccines, the uncertainties surrounding the duration of protection afforded by these vaccines, as well as the difficulty in vaccinating a large majority of the population in a timely manner, the (early) detection of COVID-19 in both unvaccinated and vaccinated individuals remains a crucial component to contain the pandemic in the future. It is expected that part of the sample will be vaccinated during follow-up. As we are interested in evaluating the experimental vs. the control condition in a real-world setting with both unvaccinated and vaccinated subjects, it is important that the V2 algorithms implemented in Period 2 are developed with vaccinated

subjects present in the Learning Phase. As such, individuals vaccinated prior to registering for the study will be eligible to enter the study, and vaccination during any period of the study will not affect ongoing participation of the subject within the study. At baseline and in the bi-weekly surveys over the course of their participation in the study, subjects will be asked whether they have received a COVID-19 vaccine (in the case of the surveys this will pertain to the preceding two weeks) and, if so, which one (see [Section 3.8](#)). Subjects that have been vaccinated during follow-up will be reminded that their participation in the study is just as vital as prior to vaccination, and will be asked to continue to follow the study procedures. They will continue to receive notifications from the Ava COVID-RED app depending on the condition that they are in and will be asked to keep getting tested when requested seeing as there is still uncertainty about the effectiveness of COVID-19 vaccinations in preventing minor or asymptomatic infection and/or further transmission of the SARS-CoV-2 virus.

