#### *Analysis sets*

Several analysis sets will be defined which will be used for the analyses described in the following sections:

- **Intention-to-treat set:** All subjects randomized to one of the two study sequences. For the analysis, subjects will be considered part of the study sequence that they were originally randomized to. Note that when a subject has their first SARS-CoV-2 infection (as confirmed through a positive PCR/antigen or serology test), they will no longer be part of the analysis going forward because they have met the primary outcome.

- **Efficacy analysis set:** All compliant subjects randomized to one of the two study sequences, where compliance is defined as having entered symptom data in the Ava COVID-RED app on at least 80% of the days of Period 2 **and**, when in the experimental condition, having worn and synchronised the Ava bracelet on at least 80% of the days of Period 2.
- **Partial compliance set:** All subjects randomized to one of the two study sequences that were partially compliant; which is defined as having entered symptom data in the Ava COVID-RED app on at least 80% of the days of Period 2 **or**, when in the experimental condition, having worn and synchronised the Ava bracelet on at least 80% of the days of Period 2.
- **Safety analysis set:** All subjects who were randomized and received an Ava bracelet.

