### 10.2 Primary Analysis of Primary Endpoint(s)

The primary analysis of the primary endpoint will compare the performance of the algorithm applied in each study condition to detect if subjects were ever infected during Period 2. This analysis will be performed on both the Intention-to-treat and Efficacy analysis sets, within each period and stratified per risk group. For the subjects within each study condition, the daily prediction of possible SARS-CoV-2 infection and the results of PCR/antigen and serology tests will be summarized over the whole period per subject to determine (1) if a subject was ever judged to have a high risk for a potential SARS-Cov-2 infection (i.e. received a red-light indicator from the Ava COVID-RED app), and (2) if a subject was ever confirmed to have a SARS-CoV-2 infection by PCR/antigen or serology testing. For this comparison, parameters such as sensitivity, specificity, positive predictive value, and negative predictive value will be calculated.

To confirm whether a subject was ever infected in Period 2 with SARS-CoV-2, the serology status at the end of Period 2 for each subject still alive at that time will be used as the gold standard. Those with a previous positive test result will be excluded from the analysis. For subjects not alive at the end of Period 2, the status of available SARS-CoV-2 virus tests during Period 2 will be used (positive at any time) and for those without any test results, a physician diagnosis during Period 2 will be accepted provided there was a supportive lung CT scan used. All other subjects will be summarized for transparency but excluded from the estimation for sensitivity, specificity, positive predictive value and negative predictive value.

The following quantities are needed for these statistics:

- **Predicted condition positive:** The total number of subjects that obtained a red-light indicator from the Ava COVID-RED app at least once during Period 2.
- **Predicted condition negative:** The total number of subjects that never obtained a red-light indicator from the Ava COVID-RED app during Period 2.
- **Condition positive:** The total number of subjects who tested positive at least once using SARS-CoV-2 virus testing during Period 2 OR who had a positive serology test at the end of Period 2.
- **Condition negative:** The total number of subjects who never tested positive for the SARS-CoV-2 virus during Period 2 AND who had a negative serology test at the end of Period 2.

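### Anti-S testing up to the end of the Learning Phase, with no exception for vaccination, would remove subjects vaccinated by then from the primary Period 2 comparison

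*Protocol*

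**What the plan says.** **Assays.** Section 3.6 says that "anti-S antibody serology tests will be used for baseline and Learning Phase samples", whereas "anti-N antibody serology tests will be used for the Period 1 and Period 2 samples". It attributes the split to short-term logistics. The same section says that approved vaccines and likely candidates "elicit an immune response against the virus spike (S) protein resulting in antibodies directed against the S-protein", that natural infection raises both anti-S and anti-N, and that "differentiation between antibodies produced following a COVID-19 vaccination or antibodies produced as a result of a natural infection by the SARS-CoV-2 virus is essential".

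**Who is tested.** Under Sections 3.6 and 8.4.8, every end-of-Learning-Phase sample is tested. A baseline sample is tested if the Learning Phase sample is positive or if the subject is a late entrant who goes straight into Period 1.

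**Vaccinated subjects.** Section 3.7 says that "individuals vaccinated prior to registering for the study will be eligible to enter the study", that vaccination during the study leaves participation unchanged, and that subjects vaccinated during follow-up keep receiving app notifications. Section 10 (general statistical approach) makes the vaccinated a key subset.

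**Consequences of a positive result.**
- Section 3.4: "When subjects obtain a positive PCR/antigen or serology test result during the study", they go into COVID-positive mode and get no more algorithm recommendations. Section 8.4.13 repeats this for a positive test.
- Section 10, intention-to-treat set: subjects with a first infection, "as confirmed through a positive PCR/antigen or serology test), they will no longer be part of the analysis going forward".
- Section 10.2: "Those with a previous positive test result will be excluded from the analysis".
- Sections 4.4 and 10.4: subjects infected in the Learning Phase contribute nothing to Periods 1 and 2.

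**The concern.** The protocol recognises that anti-S cannot tell vaccination from infection, uses it at the two earliest sampling points, and then lets a positive serology result decide infection status, app mode and entry to the primary analysis. No rule says how to read an anti-S positive in a subject known to be vaccinated.

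Two things are at stake. First, the primary Period 2 comparison would lose uninfected vaccinated subjects, although Section 3.7 wants the conditions evaluated in vaccinated and unvaccinated people alike. Second, Sections 3.4 and 8.4.13 give a vaccinated, anti-S positive subject the opposite treatment in the app from Section 3.7. This happens during conduct: Section 10.2 counts red lights actually received, and one never issued cannot be counted afterwards.

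**Working it through.** The point is textual, so the check is to follow each type of subject through the rules.

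| Subject, never infected | Tests that apply | How the rules read it | Primary Period 2 analysis |
|---|---|---|---|
| Regular entrant, vaccinated before baseline | Learning Phase anti-S positive, so baseline is tested: anti-S positive | Infected before entry | Excluded (10.2) |
| Regular entrant, vaccinated between baseline and end of Learning Phase | Learning Phase anti-S positive, baseline anti-S negative | Infected in the Learning Phase | Excluded (4.4, 10.2, 10.4) |
| Late entrant, vaccinated before baseline | Baseline anti-S positive | Infected before entry | Excluded (10.2) |
| Late entrant, vaccinated after baseline | Anti-N only | Not infected | Kept |
| Anyone first vaccinated in Period 1 or 2 | Anti-N on the later samples | Not infected | Kept |

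The table assumes that vaccination was early enough for antibodies to show. Three things follow.

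1. The stored baseline sample does not resolve the problem, because it is read with the same assay. In the second row it makes matters worse: the change from negative to positive looks like a new infection.
2. Anti-N at the end of Period 2 protects the Period 2 outcome, but a subject excluded on the earlier anti-S result never reaches that outcome.
3. Vaccination status is collected at baseline and in the two-weekly surveys (Sections 3.7, 8.4.4 and 8.4.14). The information needed to qualify an anti-S result exists, but no section links it to the exclusion or to the mode switch.

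**Size.** Section 4.4.1 bases power on 10,000 per arm in Period 2. That is the full randomised number per sequence, 20,000 / 2, so nothing is deducted for this loss. The protocol does not give the share *v* of subjects vaccinated before their last anti-S sample. With *v* assumed equal in both sequences, every such subject reading positive, and no other loss, the number left per arm is 10,000 × (1 − *v*):

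- *v* = 10%: 10,000 × 0.90 = 9,000
- *v* = 25%: 10,000 × 0.75 = 7,500
- *v* = 50%: 10,000 × 0.50 = 5,000

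These figures illustrate the range and are not estimates. No power loss is attached to them, because the protocol states no base sensitivity or specificity.

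**The case against.** The strongest reply is that the specific text should govern. Section 3.7 says that vaccinated subjects stay in and keep their notifications, Section 3.6 insists on telling the two kinds of antibody apart, and Sections 4.4, 10 (analysis sets) and 10.4 speak of infection, not of any antibody signal. On that reading a sensible team would not treat a vaccine response as an infection. This has force: the fault is unreconciled wording, not a declared intention to drop vaccinated people. But the analysis-set definition lets a positive serology test confirm infection, and Section 10.2 is worded as any earlier positive test. Someone applying those sentences as written would exclude these subjects.

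A second reply is that Section 10 plans sensitivity analyses for vaccination and leaves details to the SAP, which is not at hand. The SAP might settle the analysis side. The sensitivity analyses described do not change the primary exclusion, however, and truncating data after vaccination would remove more. A SAP also cannot restore indicators withheld during the trial.

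A third reply, that the protocol discloses the logistical limit and uses anti-N where it matters most, is correct about the Period 2 outcome but does not deal with entry to that analysis.

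A reader might infer more than the documents support:
- **That all vaccinated subjects are lost.** Only those vaccinated before their last anti-S sample are.
- **That the V2 algorithm would be trained on false infection labels.** No section says that Learning Phase serology is a training label; Section 10 speaks of physiological and symptom data.
- **That the high-risk stratum would be lost and the sample would shift to lower-risk people.** The protocol gives no order of vaccination.

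**Conclusion.** The concern holds in this limited form. As written, the protocol would classify never-infected subjects as previously infected if they were vaccinated before the end-of-Learning-Phase sample, or before the baseline sample for late entrants, and would remove them from the primary Period 2 comparison. That contradicts the aim in Section 3.7 and depletes the key subset named in Section 10. Separately, Sections 3.4 and 8.4.13 conflict with Section 3.7 on whether such subjects still receive algorithm indicators.

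The conclusion rests on the protocol's own statement that vaccines raise anti-S and on the missing exception; it needs no assumed figure. The size of the loss cannot be determined from the document. The range of 9,000 to 5,000 per arm depends entirely on an assumed share of 10% to 50%.

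**What to change.** **Analysis rule.** State in Section 10 (analysis sets) and Section 10.2 that an anti-S positive sample taken after a recorded COVID-19 vaccination does not by itself count as a previous infection for exclusion from the analysis, unless a virus test or an anti-N result confirms it. Use the vaccination data already collected. Word the Learning Phase exclusion in Sections 4.4 and 10.4 to match.

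**Supporting assays.** Where enough stored sample remains, run anti-N on the baseline or Learning Phase samples of these subjects. The protocol says that samples are stored but not how much is left after testing.

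**App mode.** Sections 3.4 and 8.4.13 must be reconciled with Section 3.7 for an anti-S positive result in a vaccinated subject. Which way to settle it is for the sponsor and the investigator.

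**Cost.** The analysis rule costs a short text change. The assays cost more as the vaccinated share rises: at an assumed 50% of 20,000 subjects, up to 10,000 subjects would be candidates. The statistical downside is that some vaccinated subjects with a true earlier infection may stay in the analysis where neither a virus test nor an anti-N result reveals it. The rule also depends on self-reported vaccination being complete.
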